### Participants

#### Inclusion criteria

(1) 18 years of age or older; (2) clinical diagnosis of psychotic disorder (F20–29), affective disorder (F30–39) or anxiety/somatisation disorder (F40–49) (International Classification of Diseases—ICD—10);^27^ (3) being hospitalised in a general adult psychiatric inpatient unit; (4) sufficient command of the language of the host country to provide written informed consent and understand the questions in the research interviews; (5) capacity to provide informed consent.

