#### Recruitment, obtaining informed consent and baseline interviews

Patients consecutively admitted to participating hospitals in each country from 1 October 2014 to 31 December 2015 are screened within two days of admission and recruited in the study. Patients will be followed-up for 1 year following their entry into the study. The end of follow-up is planned by 31 December 2016.

An internal pilot of study procedures was conducted from July 2014 to September 2014 and showed that study procedures are feasible.

First contact between the patient and the research staff takes place within two working days from the hospital admission to minimise potential selection bias due to early discharge of some patients, and to standardise the period of patient experience in the hospital. However, to ensure that as many eligible patients as possible are recruited and to increase the representativeness of the sample, there is some flexibility in recruitment. The initial contact can be postponed until the discharge if the patient wishes, or he/she is deemed to be too unwell by the clinician in charge. Before the patient is contacted by the researcher, a clinician will ask the patient for his/her assent to participate in research. If assent is obtained, the clinician introduces the researcher to the patient. The researchers explain the study and obtain written informed consent for participation in the study from the patients in face-to-face meetings. Any reason for which the interview is not conducted within two working days from the admission will be documented.

To enable an accurate estimation of selection bias, any pause in the recruitment (eg, for holidays or if all the researchers are on leave at the same time or for any other organisational reason) will be documented by specifying each day of recruitment and non-recruitment.

The overall COFI recruitment and data collection plan is reported in figure 3.

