### Analysis of clinical and social outcomes

Mixed effects models with an unstructured variance matrix will be used to assess differences in the primary outcome (rehospitalisation), and in the other clinical and social outcomes between the two groups. We will explore random effects for the hospitals or ‘specialisation’ and ‘personal continuity’ of care clusters within the hospital (in Germany, Belgium and Poland), and use fixed effects for the following covariates:
Age, gender, diagnostic group, whether or not a patient has been previously admitted, severity of illness at baseline, social situation (SIX score) and formal status of the patient at baseline.

We will check the selection bias by comparing data of our sample with the aggregate data for the total group of admitted patients during the same period.

Potential mediators of effectiveness may be: (1) the intensity of treatment, that is, sum of inpatient days and outpatient visits; (2) the experience of hospital care within the index admission, which has been shown to be predictive of better outcomes following discharge.^38^
^39^ A higher intensity of treatment or a better experience of hospital care may occur in either the ‘specialisation’ or the ‘personal continuity’ of care approach and be responsible for better outcomes.^21^
^38^ We will develop a mediation model^40^ in order to identify and explicate a potential effect of intensity of treatment and/or experience of hospital care during the index admission for assessing the effectiveness of the two approaches.^41^

Exploratory analyses to compare clinical outcomes, social outcomes and untoward events between the ‘specialisation’ and ‘personal continuity’ of care approaches will also be carried out on subgroups of patients defined by:
Age (younger or older than 40 years);Gender (males or females);Primary psychiatric diagnosis (F20–29 or F30–39 or F40–49);First or repeated admission;Socioeconomic situation (receiving state benefits due to low income or not);Migrant status (ie, country of residence different from country of birth or not);Presence of physical comorbidity/comorbidities for substance use, diabetes, cardiovascular diseases or not.

All subgroup analyses will be performed by including the relevant variables as interaction terms in the models.

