## Current study status

In June 2015, COFI is in the ninth recruitment month (out of 15 months). During the study period, 13 916 patients were admitted in the included hospitals. Among them, 8153 were eligible for the study (58.6%); 4484 of the eligible patients gave informed consent to participate in the study (55%). Eligibility and opt-in rates are similar to previous studies on hospitalised patients^38^
^50^ and the current recruitment rate is in line with the planned recruitment target (6000).

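### The selection-bias check compares the sample with all admissions, 41.4% of them not eligible, so its result cannot be attributed to non-participation among eligible patients

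*Protocol article*

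**What the plan says.** In the protocol article, the section Analysis of clinical and social outcomes gives one sentence to the analysis of selection bias. The check is made by "comparing data of our sample with the aggregate data for the total group of admitted patients during the same period". It names no variables, strata or eligible-only comparator.

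The Inclusion criteria and Exclusion criteria restrict entry by age, diagnosis (F20–29, F30–39 or F40–49), type of ward, language, organic disorder, cognitive impairment and "capacity to provide informed consent". Current study status reports that "13 916 patients were admitted in the included hospitals" by June 2015. Of these, 8153 (58.6%) were eligible, and 4484 of the eligible (55%) consented.

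The recruitment section adds a daily log of recruitment pauses, introduced with the words "To enable an accurate estimation of selection bias", and a record of why any interview was late. Under Procedures, care approach is fixed by hospital in the UK and Italy. In Belgium, Germany and Poland it is assigned to each patient from the hospital clinician's report at discharge.

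**The concern.** Selection bias through participation arises between the eligible patients and those recruited. The stated comparator is wider: it also contains everyone who failed an entry criterion. A difference between sample and comparator is then a mixture of two things, the effect of the entry criteria and the effect of who took part.

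Diagnosis shows this without any assumed figure. If any patient with a primary diagnosis outside F20–49 was admitted, the diagnostic mix of the sample must differ from that of all admissions, however participation worked.

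This matters because the study is not randomised, 45% of eligible patients were not recruited, and the Potential challenges section itself expects refusal linked to severe distress. A check meant to detect that should be able to isolate it.

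**Working it through.** **Inputs** (Current study status; interim, month 9 of 15): admitted 13 916, eligible 8153, consenting 4484.

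**Reproducing the article's percentages**
- 8153 / 13 916 = 58.6%, as stated.
- 4484 / 8153 = 55.0%, as stated.

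**The three groups inside the comparator**
- Recruited: 4484 / 13 916 = 32.2%.
- Eligible, not recruited: 8153 − 4484 = 3669, which is 26.4% of admitted and 45.0% of eligible.
- Not eligible: 13 916 − 8153 = 5763, which is 41.4% of admitted.

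**What the check measures.** Let s, r and i be the prevalence of a trait in the recruited, the eligible not recruited and the ineligible. The prevalence in all admissions is 0.322 s + 0.264 r + 0.414 i, so

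sample − all admitted = 0.264 (s − r) + 0.414 (s − i).

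The contrast of interest is

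sample − all eligible = 0.450 (s − r).

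Only the first term of the planned check concerns participation. The second has the larger weight: 0.414 / 0.264 is about 1.6. One difference cannot be separated into its two terms.

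**Two illustrations.** The prevalences are assumed and are not in the documents.
- *False alarm:* s = r = 30%, i = 50%. Check: 0.264 × 0 + 0.414 × (−20) = −8.3 points. Participation is not selective at all.
- *False reassurance:* s = 30%, r = 45%, i = 20.45%. Check: 0.2637 × (−15) + 0.4141 × 9.55 = −3.95 + 3.95 = 0.0 points. Yet the sample differs from the eligible group by 0.450 × (−15) = −6.8 points.

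The second case is tuned to cancel exactly, which happens when s − i = −0.637 (s − r), with 3669 / 5763 = 0.637. Partial cancellation needs only that the two terms have opposite signs.

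**Why a breakdown helps.** If selection were −5 points under one approach and +5 under the other, in equal groups, a single overall figure would be 0 while the approaches differed by 10 points. This is again an assumed example.

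**The case against.** Several points on the other side stand.

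- **Split by approach.** A reader might infer that the check is pooled over the two approaches. The article does not say so. It is one sentence in a condensed article, silent on strata, and in the UK and Italy a table by hospital would already be a table by approach.
- **Deliberate exclusion.** A reader might also infer that all 5763 were excluded on purpose and are irrelevant. The reasons are not given. Some may have lacked capacity, and the Potential challenges section says many patients may be unable to consent. For representativeness of all inpatients, which the recruitment section names as an aim, comparison with all admissions is legitimate.
- **The eligible count is not clean.** Screening takes place within two days of admission, but the primary diagnosis is established at discharge. First contact may be postponed until discharge, so some of the 3669 may not yet have been approached.
- **Other safeguards.** Recruitment pauses and reasons for late interviews are logged. The primary model adjusts for age, gender, diagnostic group, previous admission and formal status, so weights built only on those items would largely repeat that adjustment.
- **Size.** The illustrations show what is possible; they do not estimate anything in this study.

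None of this makes the stated comparator suitable for its stated purpose. The logs document the recruitment process but do not compare participants with non-participants. Model adjustment does not report how participation differed. Uncertainty about why patients were ineligible is a reason to show that step separately.

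**Conclusion.** The point holds in limited form. The article fixes a comparator of which 41.4% was not eligible at the interim count. A difference, or its absence, cannot then be attributed to non-participation among the 8153 eligible patients, 45.0% of whom were not recruited. This is a stated method with a better alternative, not a detail left to another document.

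The percentages come from the article and will change by the end of recruitment. The 8.3-point false gap and the 6.8-point hidden gap rest on assumed prevalences.

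It would go too far to conclude that the comparison of approaches is biased, or that bias between approaches cannot be examined. The first depends on whether selection differs between approaches or interacts with the effect, and the documents give no data on either. The second is not ruled out by the text. The primary model and the sample size are unaffected.

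**What to change.** Replace the single comparison with two reported steps.

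1. **Admitted versus eligible**, with counts and reasons for ineligibility, incapacity shown separately. Present this as a description of representativeness.
2. **Recruited versus eligible but not recruited**, as the selection-bias check. Use routinely recorded items such as age, gender, diagnostic group, first or repeat admission and formal status. State whether diagnosis is taken at screening or at discharge. If non-recruited patients cannot be separated, compare recruited with all eligible. If only aggregate hospital data exist, restrict them at least to admissions meeting the age and diagnosis criteria.

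Tabulate both steps by country and hospital. In the UK and Italy this gives the comparison by approach. In Belgium, Germany and Poland the article describes no way to assign approach to non-participants, so report by hospital and state that limit.

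A sensitivity analysis weighted to the margins of the eligible population is optional and depends on the data held. The article mentions only aggregate data, so individual-level participation weights should not be assumed feasible.

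The cost is modest extra tabulation. Eligible patients are already counted; whether their characteristics are held by eligibility status has to be confirmed with the sites.

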#### Primary outcome

Readmission to hospital.

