#### Other clinical and social outcomes

*Clinical outcomes* including: (1) number of readmissions; (2) number of compulsory readmissions; (3) inpatient bed days, using an ad hoc schedule based on the Client Service Receipt Inventory.^30^*Social outcomes,* based on the SIX index,^31^ which captures*:* (1) employment (none; voluntary or protected or sheltered work; regular employment); (2) accommodation (homeless or 24 h supervised; sheltered or supported accommodation; independent accommodation); (3) living situation (living alone; living with a partner or family); (4) contacts with friends (not having met a friend within the past week; having met at least one friend in the past week).*Subjective quality of life*, measured by the Manchester Short Assessment of quality of life MANSA.^32^*Untoward incidents related to mental healthcare*, including: (a) deaths; (b) completed suicides; (c) serious assaults committed by patients; (d) physical violence experienced by patients; (e) suicide attempts; (f) serious side effects from pharmacological treatment requiring hospitalisation, as extracted from clinical records or obtained through phone interviews.*Social contacts,* measured as: (a) the total number of social contacts within the week preceding the assessment as reported by patients using an ad hoc instrument, adapted from the Social Network Schedule,^33^ and (b) whether or not they declare to have at least one close friend, using the specific item on the MANSA.^32^*Experienced discrimination,* measured as*:* (a) patient-reported episodes of discrimination because of mental illness, and (b) patient-reported avoidance of activities because of fear of discrimination, measured by ad hoc items.*Perceived socioeconomic status,* that is, patient self-rated standing in his/her own self-defined community and country, measured by the MacArthur Scale of Subjective Social Status.^34^
^35^

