#### Costs

Service use will be measured using an adapted version of the Client Service Receipt Inventory.^30^ This will include details of:
In-patient bed days;Contacts with outpatient services;Contacts with day centres;Contacts with other community services.

We will then calculate unit costs for each service and for the different countries in order to translate service use data into costs of care.

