### Analysis of costs

The economic analysis will be led by the Centre for the Economics of Mental and Physical Health at King’s College London. Unit costs for each service measured with the CSRI will be calculated for each country. In order to compare costs across countries with different currencies, purchasing-power parities will be used to transform the country-specific costs into a single currency, thus allowing for analysis of the total sample as well as cross-national comparisons. The likely different impact of cost externalities or different cost structure of the two care approaches will be evaluated. Multiple regression will be used to adjust for the baseline patient characteristics in all tests of differences in costs and clinical outcomes. Cost-effectiveness will be then explored through the calculation of incremental cost-effectiveness ratios (ICER), defined as the difference in mean costs divided by difference in mean effects.

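### The treatment-intensity mediator adds bed days to outpatient visits one for one, which dilutes any pathway through outpatient contact; the two parts should enter the mediation model separately

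*Protocol article*

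**What the plan says.** Under the data analysis plan, in the section on the analysis of clinical and social outcomes, the protocol lists two candidate mediators. One is "the intensity of treatment, that is, sum of inpatient days and outpatient visits"; the other is the patient's experience of care during the index admission. It then announces the analysis: "We will develop a mediation model", to cover either or both. The motivation given is that "A higher intensity of treatment or a better experience of hospital care may occur in either" approach and could account for better outcomes, so the plan expects more intensity to go with better results.

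No section weights, standardises or separates the two parts for this model. The list under Costs nevertheless records them as distinct items: "In-patient bed days;Contacts with outpatient services;Contacts with day centres". Bed days also appear among the follow-up outcomes as "inpatient bed days, using an ad hoc schedule based on the Client Service Receipt Inventory", and the primary outcome is "Readmission to hospital". The mediator definition does not say whether its inpatient days are those of the index stay or those of the follow-up year.

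**The concern.** A bed day is 24 hours of care and a visit is a single contact, yet each adds one unit to the mediator. A model with one coefficient on the sum assumes that both have the same effect on readmission, and nothing in the protocol supports that. They could well differ: outpatient contact might prevent readmission, while a long stay might mark more severe illness. Ten visits in place of ten bed days leave the mediator unchanged, although the study is about how care is organised across the inpatient and outpatient settings.

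At stake is the explanation of any difference between the approaches. If part of a true effect ran through outpatient contact, the summed mediator could miss most of it and leave it in the direct effect.

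**Working it through.** The protocol gives no figure for this mediator and no mean or SD for bed days or visits. All numerical inputs below are therefore assumptions, shown over a range.

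**Notation.** D is inpatient days and V outpatient visits, with SDs σD and σV. βD and βV are log-odds of readmission per day and per visit. aD and aV are the changes that the approach makes in each.

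- Indirect effect with separate mediators: aD·βD + aV·βV.
- Indirect effect through the sum: (aD + aV)·βS. For uncorrelated parts, in linear approximation, βS = (βD·σD² + βV·σV²)/(σD² + σV²).
- If bed days have no effect and do not move (βD = 0, aD = 0), the fraction recovered is σV²/(σD² + σV²), the visits' share of the variance of the sum.

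**Closed form.** Assume σV = 10, βV = −0.3/10 = −0.03 per visit, aV = 5 and aD = 0. The true indirect effect is 5 × (−0.03) = −0.15. In the right-hand column bed days raise the log-odds by 0.2 per SD.

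| σD | Sum, bed days no effect | Sum, bed days +0.2 per SD |
|---|---|---|
| 10 | 5 × (−3)/200 = −0.075 (50%) | 5 × (2 − 3)/200 = −0.025 |
| 20 | 5 × (−3)/500 = −0.030 (20%) | 5 × (4 − 3)/500 = +0.010 |
| 40 | 5 × (−3)/1700 = −0.009 (6%) | 5 × (8 − 3)/1700 = +0.015 |
| 60 | 5 × (−3)/3700 = −0.004 (3%) | 5 × (12 − 3)/3700 = +0.012 |

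**Range over spreads.** For bed-day SDs of 10 to 60 and visit SDs of 5 to 20, uncorrelated, bed days supply 20% to 99% of the variance of the sum. With no bed-day effect, that means 80% down to 1% of a visit pathway is recovered.

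**When the sign changes.** With aD = 0, reversal requires βD·σD² > |βV|·σV². At σD = 10 in the right-hand column, 0.02 × 100 = 2 is below 0.03 × 100 = 3, so there is no reversal. At σD = 20, 0.01 × 400 = 4 exceeds 3, and the sign flips.

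The other route is movement in opposite directions. Take equal SDs of 10, βD = 0, five more visits and ten fewer bed days. Then βS = −3/200 = −0.015, and the sum gives (5 − 10) × (−0.015) = +0.075, against a true −0.15.

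**Simulation with other inputs.** Logistic outcome model, gamma-distributed counts, 200,000 patients, about 30% readmitted, three more visits under one approach, βV = −0.05. The last two columns are indirect effects.

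| Bed-day SD / visit SD | βD | Change in bed days | Via visits, separate mediators | Via the sum |
|---|---|---|---|---|
| 30 / 8 | 0.015 | 0 | −0.149 | +0.035 |
| 30 / 8 | 0 | 0 | −0.150 | −0.009 |
| 30 / 8 | 0.015 | −3 | −0.149 | −0.002 |
| 10 / 8 | 0.015 | 0 | −0.154 | −0.024 |
| 10 / 15 | 0.015 | 0 | −0.145 | −0.063 |
| 10 / 15 | 0 | 0 | −0.146 | −0.084 |

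In the third row a further −0.047 runs through bed days when they are separate; in the sum the two movements cancel. Across the six settings the sum reversed the sign once, came out near zero twice, and kept the right sign but shrank three times. The closed form is only approximate for a logistic model with skewed counts: in the last row it predicts 225/325 = 69% recovered, and the simulation gave 0.0835/0.1455 = 57%.

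**The case against.** The best defence is that the plan asks about total intensity, not about a pathway through outpatient contact. On that reading, a swap of ten bed days for ten visits is meant to count as no change. This stands in part, since the choice of construct belongs to the investigators. But a total-intensity question does not require equal effects per day and per visit. The joint indirect effect of two mediators answers it without that restriction.

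The wording is also tentative, the analysis is not the primary one, and a journal article leaves detail to a fuller plan. That limits the weight of the point. It does not remove it, because the article states the definition outright.

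The magnitudes rest on assumed spreads. That stands fully: if visits vary as much as or more than bed days, an effect through visits alone is diluted, and reversal then requires a correspondingly large opposite effect per bed day.

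A reader might infer that the mediation result will have the wrong sign, or that the study's recommendations would then be wrong. The documents support neither. Reversal needs the extra conditions shown in the working. The introduction says that continuity may ease movement between settings, not that visits replace bed days. The section on expected outputs bases recommendations on the study's findings in general and does not tie them to the mediation model.

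**Conclusion.** The point holds as a weakness of a stated definition, confined to the secondary mediation analysis. The unweighted sum imposes a common effect on two unlike quantities and cannot show a shift between them; that conclusion needs no assumed figures. How much is lost does need them: half of a visit pathway with equal, uncorrelated SDs and no bed-day effect, and more as bed days become the more variable part. Loss is the general expectation and a changed sign a special case. The comparison of readmission between approaches and the sample size are unaffected. This is a cheap improvement, not a threat to the study's main conclusion.

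**What to change.** In the section on the analysis of clinical and social outcomes, replace the sum by two mediators in the same model, inpatient days and outpatient visits. Report the indirect effect of each and the joint indirect effect. State that the inpatient days are those of the index stay. If follow-up days were used, the mediator would contain readmission days, which are part of the outcome it is meant to explain. The simple sum can stay as a secondary description.

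An index weighted by unit costs is not a good substitute, although the section on the analysis of costs makes it look available: "Unit costs for each service measured with the CSRI will be calculated for each country". If a bed day costs more than a visit, the weighting increases the dominance of bed days. Counting a day as two visits turns an SD of 20 into an effective 40, and recovery in the closed-form example falls from 20% to 6%. Country-specific unit costs would also make the weights differ between countries unless they were harmonised.

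The cost is one extra mediator and a change of wording. The Costs list already records the two parts as separate items. The downside is slightly less precise individual indirect effects if days and visits are correlated.

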### Baseline measures

At baseline, we will collect data on:
Sociodemographic characteristics: year of birth, gender, marital status, highest completed education level, country of birth;Social situation: employment, accommodation, living situation, friendships, self-reported benefits receipt due to low income;Psychiatric and non-psychiatric diagnoses according to the International Classification of Disease 10 (ICD-10);^27^ the primary clinical diagnosis is established from medical records or clinician’s report at discharge from hospital;Severity of illness, rated by treating psychiatrists by the Clinical Global Impression Scale (CGI);^28^Whether the current admission is the first one or not;Formal status at admission (involuntary/voluntary);Patient appraisal of inpatient care, as measured by the Client Assessment of Treatment (CAT).^29^

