### Sample size determination

The sample size for the quantitative study was calculated with the aim to detect a 5% difference in rates of re-admissions (ie proportion of patients re-hospitalised during the one year follow up) between the two care approaches from 27.5% to 32.5% with 80% power at the 5% significance level.

The sample size required for an individual-level comparison not considering clustering of outcomes within centres and hospital would be 2716 patients.

We calculated an average cluster size per hospital of 150 patients recruited over one year. Taking into account a 15% drop out rate, the average number per hospital of patients recruited and followed up will be 128. The variance inflation factor (or design effect, IF) is given by IF=1+(m−1)×ρ; where m=cluster size, and ρ=ICC (inter-cluster correlation coefficient). The ICC in a cluster with such a large number of patients is expected to be very small.^37^ With m=128 and ρ=0.007, IF is 1.90, and the adjusted sample size is N=5162 (1034 per country), requiring eight hospitals per country with an average number of 150 patients recruited per hospital, ie 1200 patients per country and 6000 overall.

We will carry out follow-up face-to-face interviews with a subsample of patients who will be 18–65 years of age. The patients will be stratified based on diagnostic group (ICD codes: F20–29, F30–39, F40–49)^27^ and on whether the index admission was their first one or they have had previous hospital admissions. We will aim to interview 30 patients per stratum, resulting in 360 patients per country (60×6 clusters) and an overall sample of 1800 patients (360×5 countries).

For the in-depth interviews, we will purposively select 40 patients and 13 clinicians in each country, resulting in a total sample of 200 patients and 65 clinicians.

Within the sample, there will be a mix of: (1) patients treated with ‘specialisation’ and ‘personal continuity’ of care approaches; (2) those who were rehospitalised during the follow-up and those who were not; and (3) patients with different diagnoses (F20–29, F30–39, F40–49).

Clinicians will be included taking into account: (1) the care approach (‘specialisation’ or ‘personal continuity’) adopted by the service they work within and (2) their qualification: psychiatrists, psychologists, nurses/social workers.

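### The exploratory approach-by-age interaction splits age at 40, which weakens the test if the approach effect changes roughly linearly with age

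*Protocol article*

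**What the plan says.** The relevant text is in the protocol article, Data analysis plan, Analysis of clinical and social outcomes.

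- The subgroup comparisons are introduced as "Exploratory analyses to compare clinical outcomes, social outcomes and untoward events" between the two approaches. Age heads the list of seven subgroup variables, as "Age (younger or older than 40 years".
- On method: "All subgroup analyses will be performed by including the relevant variables as interaction terms in the models".
- The same section lists age, with no cut, among the fixed-effect covariates of the mixed models: "Age, gender, diagnostic group, whether or not a patient has been previously admitted, severity of illness at baseline". It does not say whether that covariate enters as continuous.

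Under Baseline measures the data collected include "year of birth, gender, marital status, highest completed education level, country of birth", so age in years can be derived. Under Inclusion criteria the full sample is "18 years of age or older", with no upper limit.

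**The concern.** The split at 40 is a stated choice, not a detail left open. It amounts to assuming that the difference between the approaches is constant from 18 to 39, changes at 40, and is constant from there to the oldest patient. The chosen method does not call for this, because an interaction term accepts a continuous variable. As the article describes the seven subgroup variables, age is the only one that is a continuous measurement cut at a number. The others are categories or yes/no items.

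What is at stake is whether the study can see that the better approach depends on age. The Introduction section of the Abstract asks whether effectiveness varies between patient groups, and Aims and objectives names age among the subgroups. If the effect drifts gradually across adult life, a two-group contrast is a weaker test on the same patients.

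**Working it through.** **1. The plan's own figure.** The article gives no power for any interaction. Its sample size concerns only the overall readmission comparison, "from 27.5% to 32.5% with 80% power at the 5% significance level". A two-sided test is assumed.
- Pooled-variance formula: n per arm = [1.96·√(2·0.30·0.70) + 0.84·√(0.275·0.725 + 0.325·0.675)]² / 0.05² = 1318, or 2636 in total.
- With the continuity correction: (1318/4)·[1 + √(1 + 4/(1318·0.05))]² ≈ 1358 per arm, or 2716 in total. This matches the article exactly.
- Design effect: 1 + 127·0.007 = 1.889. Then 2716·1.889 = 5131, and with the rounded 1.90 it is 5160, against 5162 stated. This agrees within rounding.

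So the main calculation reproduces, and it makes no claim about age.

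**2. Information kept by the cut.** If the approach effect is linear in age, the efficiency of the two-group interaction relative to the continuous one is

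RE = [corr(age, I(age ≥ 40))]².

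The age distribution is an assumption throughout:

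| Assumed age distribution | RE | Information lost |
|---|---|---|
| Normal, split at its median (2/π) | 0.637 | 36% |
| Truncated normal 18-85, nominal mean 38, SD 12-16 | 0.66 | 34% |
| Truncated normal 18-85, nominal mean 42, SD 13 | 0.638 | 36% |
| Truncated normal 18-85, nominal mean 45, SD 12-16 | 0.60-0.61 | 39-40% |
| Uniform 18-65 | 0.747 | 25% |
| Uniform 18-80 | 0.687 | 31% |

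The working range is therefore about 25-40%. With an older sample (realised mean about 46-49) the loss reaches 41-48%, because 40 then lies further from the centre.

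**3. Effect on power.** Where continuous age has 80% power at two-sided 5%, the cut has power Φ[(1.96 + 0.84)·√RE − 1.96]:
- RE 0.60: 58%
- RE 0.637: 61%
- RE 0.75: 68%

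At RE 0.637, equal power would need 1/0.637 = 1.57 times the sample.

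**4. Worked example (illustrative, ignoring clustering).** Take 5100 analysed patients in equal groups, 30% readmitted, an approach effect that changes by 10 percentage points over 30 years of age, and truncated-normal age (nominal mean 42, SD 13, realised SD 12.0).
- SE of the slope difference = √[4·0.21/(5100·12.0²)] = 0.00107.
- Continuous age: z = (0.10/30)/0.00107 = 3.11, power 88%.
- Cut: z = 3.11·√0.638 = 2.49, power 70%.

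**5. Check by simulation.** Logistic interaction models with N = 5100 and a linear interaction, 400 replicates for each of two age distributions, gave 61-62% of the information kept. Power was 0.74-0.76 with continuous age and 0.51-0.54 with the cut. Leaving continuous age in the model as a main effect did not recover the loss.

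**6. When the cut is not worse.** Under the same age distribution (nominal mean 42, SD 13), the squared correlation of each test variable with the true pattern of effect is:

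| True pattern of the approach effect | Cut at 40 | Linear age |
|---|---|---|
| Step at 37 | 0.68 | 0.59 |
| Step at 40 | 1.00 | 0.64 |
| Step at 43 | 0.68 | 0.66 |
| Ramp from 35 to 45 | 0.90 | 0.77 |
| Ramp from 30 to 45 | 0.83 | 0.78 |
| Ramp from 25 to 45 | 0.76 | 0.78 |
| Ramp from 35 to 50 | 0.81 | 0.84 |
| Ramp from 30 to 50 | 0.81 | 0.87 |

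The cut is better for steps near 40 and for narrow ramps around it. The two are close for ramps of 15-20 years reaching 45 or 50. The linear term gains clearly only as the change spreads over most of the adult range.

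**The case against.** The strongest reply is that these analyses are labelled exploratory and that the sample size statement powers only the overall readmission comparison. Age is also not a hypothesised modifier: the two hypotheses in Aims and objectives concern complexity of need, severe illness, comorbidity, socioeconomic status and migration. The cut is prespecified, so it is not chosen from the data. It matches the categorical form of the other subgroups and gives group-specific estimates that policy readers can use. A linear term imposes a shape of its own.

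All of that stands, and it limits the weight of the point. It does not supply a reason to prefer the split as the test. Exploratory status governs how firmly a result is read, and the ease of reading two groups is kept if the split remains as a display. The objection to linearity is met by allowing a simple spline.

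A reader might infer more than the document supports:
- That a third of the information is lost as a matter of fact. The article gives neither an age distribution nor a shape of effect, so the loss is conditional on both.
- That the cut wins only if the effect steps exactly at 40. Step 6 of the working shows that it also wins for nearby steps and some gradual changes.
- That the missing reason for 40, or the wording about patients aged exactly 40, is a defect. A condensed article commonly leaves such details to the full plan.
- That a continuous age term is already in the model. The covariate is listed without a cut, but its form is not stated.

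**Conclusion.** The point holds as a minor improvement. If the approach effect changes roughly linearly across the adult age range, splitting age at 40 loses about 25-40% of the information on the approach-by-age interaction, and a test with 80% power on continuous age falls to about 58-68%. The size rests on assumed age distributions (more if the sample is older), on equal groups and on near-linearity. The advantage shrinks or reverses if the effect changes abruptly or over a narrow band near 40. One of seven exploratory subgroup variables is affected. The primary analysis and its sample size are not.

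**What to change.** In Analysis of clinical and social outcomes, state that the approach-by-age interaction will be tested with age as a continuous variable, either linear or as a simple spline so that linearity is not imposed. Report the estimated approach effect with its confidence interval at a few ages, for example 25, 40 and 60. Keep under 40 versus 40 and over as a descriptive display, which also places patients aged exactly 40.

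The cost is one line of analysis wording and no new data. There are two small downsides. A linear term is less sensitive if the effect changes abruptly or over a narrow range around 40. A continuous interaction also takes slightly more work to present. The spline option addresses part of the first, and the retained display helps with both.
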